### 2.2. Study Population

The participants in this study will be categorized into three groups: the MTs, the teachers and the adolescents. Firstly, a selected group of three experienced educators/trainers who will act as MTs will be recruited. These individuals will be responsible for training the school teachers and overseeing the fidelity of the intervention delivery. MTs will undergo training sessions on tobacco prevention, facilitation techniques, and the “If–Then” planning methodology. Based on their new knowledge and skills, MTs will conduct training sessions and provide feedback and support to teachers throughout the implementation phase. Secondly, school teachers will be selected to participate in the intervention. These teachers will be trained by the MTs to deliver the tobacco prevention intervention to the adolescent participants. All teachers from the participating schools (approximately n = 250) will be invited to participate in the program. However, as this is a pilot intervention, the first four to five teachers from each school will be accepted to participate in the study, resulting in a total of 20 to 25 participants. The first-come, first-served approach was primarily adopted for pragmatic reasons, aligning with the goals of a pilot implementation study. Firstly, as this is an initial feasibility and implementation protocol, the main objective is to determine if the intervention can be successfully delivered by willing teachers in a real-world setting, rather than to recruit a perfectly representative sample. Secondly, restricting participation to 4–5 teachers per school creates a practical and manageable group size for the intensive training provided. Nevertheless, and considering that each classroom includes around 20 students, we anticipate that the intervention will reach approximately 480 adolescents.

#### 2.2.1. Selection and Preparation of Country MTs (Phase I)

Three MTs will be selected with a strong background in public health, applying facilitation techniques and addressing the diverse challenges faced by adolescents. The selected MTs will be required to be motivated and tobacco-free individuals with a proven dedication to adolescent engagement. MTs need to have completed the IPCRG’s Teach-the-Teacher (TtT) program adapted to facilitate the “Implementation Intentions” intervention. The program was conducted by IPCRG from November to December 2024 and featured interactive online sessions covering numerous topics, such as “Behaviour Change with a Focus on Adolescents”, “Teaching Skills (Learning Needs, Objectives, and Methods)”, and “The If-Then Approach and Peer Learning”. [46]. This training empowered participants to more effectively train the school teachers by transferring both the knowledge and the pedagogical techniques necessary for delivering our intervention.

Given the overlapping roles of Master Trainers in adaptation, training, and evaluation, they will document their assumptions, and roles will be clarified so that those adapting the training are not solely responsible for its evaluation. Specifically, all MTs will keep a structured adaptation logbook detailing each procedure (adaptation, training of teachers, evaluation, etc.). Moreover, MTs will focus primarily on delivery and teacher training and support, while different research team members will conduct data collection, evaluation, and analysis. Furthermore, an independent FRESHAIR4Life member will oversee all processes, receive regular updates from country team members, assess their progress, and offer feedback.

#### 2.2.2. Selection of School Teachers

Teachers will be invited to participate in the intervention through outreach visits by the MTs at the schools. These visits will include face-to-face meetings with headmasters and teachers and lectures/presentations in six schools. To be eligible, teachers must be employed at a participating school, willing to attend both training sessions, willing to deliver the program to their classes, and able to communicate effectively in Greek. No exclusion criteria were predetermined for teachers.

#### 2.2.3. Selection of Students

The intervention’s target demographic is middle- and high- school students (age: 13–16 years), with the participating school teachers acting as implementers. Initially, lectures will be scheduled at all selected schools to present information on smoking prevalence, effects, and the planned intervention with headmasters, teachers, and parents invited. These lectures, presented by the MTs, will inform and clarify the intervention to participating teachers and parents, thereby encouraging parental support for student participation. Then, the headmaster or a representative teacher from each school will inform all parents/legal guardians of the adolescents about the program. The students to be included should be enrolled in the classes of the trained teachers (implementors). Each student will be given an information sheet (outlining the study), an informed consent form for their legal guardian to sign, and an assent form for them to sign. All students in the participating classes will receive the intervention, though they have the option to decline participation in its evaluation. To be eligible for the evaluation of the intervention, participants must have the ability to understand the Greek language, agree to participate in the evaluation (by signing the informed assent) and to have the consent of a parent or a guardian (by signing the informed consent). Students who do not provide signed assent and consent forms will be excluded from the evaluation and will engage in a separate activity with the headmaster (smoking prevention-related) outside the classroom during the evaluation.

### 2.3. Adaptation of the Material by the MTs (Phase II)

The “If–Then” intervention was originally developed for adolescents in the UK, aged 11–15, with sessions lasting two hours per year for four consecutive school years, delivered in school settings by teachers [27,29,31,47]. However, for its implementation in Greece and for our study, several modifications will be required to accommodate the distinct sociocultural context. In addition, the target age range was adapted from the original 11–15 (Intent’s age range) to 13–16 years. This was intentional, since in the structure of the Greek secondary school system, middle school enrolls students aged 13–15, while high school covers ages 15–18. As students aged 11–12 do not attend Greek secondary schools, they are not accessible within a middle school-based delivery model, making the 13–16 range both appropriate and operationally necessary. The overall cultural adaptation process was guided by the principles of systematic intervention adaptation (including stakeholder engagement, iterative review, and piloting), while AACTT (Actor, Action, Context, Target, Time) was applied specifically to specify and articulate the key behaviors targeted by the intervention [44]. The adaptation process will involve a collaborative effort with key stakeholders, including teachers, behavioral experts, and a representative group of adolescents. For this reason, a meeting with the three selected MTs, one secretary (for log keeping), and at least four (4) middle school teachers, four (4) high school teachers, and ten (10) adolescents (14–16 years old), will be held to adapt the materials. The meeting agenda will include the timing of the implementation, the number and duration of sessions, the review and selection of the most appropriate INTENT materials and pilot testing of the material. Teachers and students will jointly discuss and agree on both the selection of the materials and the rationale behind these choices. After a comprehensive review of all materials, the participants will discuss the adaptation process. An adaptation log will be used to document decisions about changes, including the proposed modifications, the justification for them, and the stakeholders who will have participated. These proposals will then be discussed in stakeholder meetings, with agreements or concerns captured in brief minutes. Decisions will be finalized via consensus and documented in a protocol to guarantee transparency and traceability.

The research team (co-authors of this paper), to facilitate the adaptation process, has already discussed and agreed that the original UK session structure should be reduced from eight to two sessions (80–90 min each), and incorporate language and visual adjustments while expanding session content to encompass TU vaping and nicotine pouch use in addition to cigarette smoking, due to the high prevalence of use by Greek adolescents. Furthermore, a written supplementary resource will be developed to guide teachers in addressing and supporting students with existing TU who may wish to quit.

### 2.4. The Implementation

The intervention will be conducted in two phases (Table 1). The first phase will prepare the participating teachers to utilize the material. The second phase will involve the implementation of the material by the teachers in their classrooms.

#### 2.4.1. Preparation Phase—Teaching the Volunteer Teachers (Phase III)

Teachers will participate in an intensive training program led by the selected MTs. The training will be divided into two separate structured training sessions, one held online and one face-to-face (Table 2). Both of these sessions will be delivered by the MTs, approximately one to two weeks prior to implementation. The first session (about one hour), will be held online by the MTs, who will present teachers with all the adapted and translated INTENT materials, including session guides, presentations (power point format), explanatory videos, and relevant resources, through the “Google Classroom” platform. Specifically, the MTs will introduce the program’s targets, the importance of addressing adolescent TU, and the theoretical background behind the “If–Then” implementation (e.g., “If I’m offered a cigarette, then I’ll say I don’t smoke because it affects my asthma”), while also answering questions [46]. The second session will consist of a one-hour workshop held in the school environment in each of the six participating schools (4–5 teachers in each school), where MTs will guide teachers through all the necessary techniques for a successful implementation of the intervention. The workshop will build on the foundation established in the first session, providing a hands-on experience to refine teachers’ abilities to deliver the intervention with active learning techniques. These techniques usually include open-ended questioning and active listening, practicing in pairs. Furthermore, teachers will participate in role-plays addressing common challenges of adolescents, such as peer pressure, vaping myths and truths, or students who face difficulty engaging with others. After each role-play, the group participates in a debrief, discussing what worked well and identifying areas for improvement. Each teacher will deliver a short practice segment of the intervention and will receive structured feedback from both MTs and colleagues, and will repeat the activity to refine pacing, clarity, and interaction skills, incorporating the feedback they received.

#### 2.4.2. Implementation Phase of the Study—Teachers Utilizing the Intervention at Their Classrooms (Phase IV)

The second phase of the intervention will be based on the deliverance of the “Implementation Intentions” intervention by the teachers at the schools. The implementation, as mentioned above, will be conducted in six different schools and will consist of two structured sessions (Table 3). Both sessions, each lasting two school hours (~90 min), will be delivered by trained teachers, scheduled approximately two months apart. MTs will oversee all sessions and assist teachers where needed. In the first session, teachers will introduce our intervention to students. Introducing our intervention, teachers will explain that through this program students will have the opportunity to explore the factors in their life that may influence them to smoke. Teachers will highlight the fact that committing to do something by putting this commitment down on paper is much more likely to result in success, by creating a “Personal Plan (PP)”. This session includes interactive conversations with students addressing myths and truths about TU and the long-term effects of initiating smoking, as well as quizzes regarding TU. The first session will conclude with a written exercise outlining each student’s refusal tactics, followed by the development of their Personal Plans (PPs). The second session aims to strengthen students’ personal resilience and highlight the complexity of external influences on their decision to remain smoke-free. Moreover, teachers will examine what students can recall from the previous lecture. Students will be informed about how smoking interplays with stress and once again, they will create their PP. It should be noted that both quantitative and qualitative data will be collected by the MTs, before, during and after the intervention.

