### 2.5. Data Collection (Phase V)

Data collection for this study will be organized around the intervention. First, students and teachers will complete quantitative questionnaires. These will be given at two points, (1) before the intervention (baseline) and (2) after the two sessions (post-intervention follow-up). Second, fidelity and implementation-related data will be collected during the intervention (session logs and observational checklists). These will be collected between the two sessions. Third, qualitative data will be collected after the intervention. This will involve semi-structured interviews and focus groups with participants (students and teachers). Moreover, team-members (other than MTs) will collect the data at each phase of the intervention. As stated, both quantitative (questionnaires) and qualitative data (interviews and FGs) will be collected for this study. The questionnaires will be developed for this and will consist of closed and open questions presented in a structured format. Specifically, close-ended questions will be either Likert-type (rated 1-almost never to 5-almost always) or dichotomous (yes or no). Each question will yield a score, and these scores will be summed for a total. Higher total scores will indicate a greater level of the measured variable. The estimated time for completing both the questionnaires and the interview is approximately 60 min.

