#### 2.5.3. Qualitative Data Collection for Teachers, MTs, and Students

Qualitative data from students (Table 4), MTs, and teachers (Table 5) will be collected through semi-structured interviews, focus groups and open-ended written questions, post-intervention. Following the intervention, MTs will organize semi-structured interviews or focus groups, inviting participation from students and teachers (at least 3–4 students and 2–3 teachers from each school), separately. These interviews/focus groups will explore the perceived effectiveness, cultural relevance of intervention, ease of understanding, and areas for improvement. Regarding the MTs, a FRESHAIR4Life team member will interview them in a semi-structured format about their experience organizing the intervention, any difficulties they encountered, and suggestions for improvement in future implementations.

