### 2.7. Data Analysis

Quantitative data will be analyzed using the IBM SPSS 29 program. Descriptive statistics will summarize participant characteristics and engagement metrics. Paired *t*-tests and regression analyses will evaluate changes in the tobacco-related behaviors and attitudes of the participating students. Multiple linear regression analysis will be used to assess the strength and direction of the relationships between variables across the implementation period. As this study is exploratory, *p*-values will be interpreted alongside effect sizes and 95% confidence intervals. These will be the primary indicators of the strength and precision of the potential associations found. Specifically, Cohen’s d will be reported for paired *t*-tests, and standardized beta coefficients (β) for regression analyses. Statistical significance will be set to *p* < 0.05.

Interviews/focus groups will be audio-recorded, transcribed, and analyzed thematically by the MTs. More specifically, qualitative data will be analyzed using Braun and Clarke’s six-step framework for thematic analysis (Braun and Clarke) [50]. This involves transcribing and thematically analyzing the interviews and focus groups. First, the process involves verbatim transcription of audio-recorded interviews and focus groups, followed by multiple readings to understand the content. The transcripts will then be coded inductively (allowing themes to emerge) and deductively (focusing on study-specific aspects like adherence and quality of life). Codes will be grouped into categories, then refined into broader themes and subthemes. Finally, these themes will be presented with supporting quotes, and the qualitative findings will be triangulated with quantitative data to identify convergence or divergence between measurable outcomes and self-reported experiences [51].

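### The protocol contradicts itself on whether the Master Trainers or other team members collect the data and analyse the interviews

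*Protocol article*

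**What the plan says.** Section 2.2.1 of the protocol article acknowledges that the MTs have overlapping roles in adaptation, training and evaluation. It says roles will be clarified so that "those adapting the training are not solely responsible for its evaluation", and then makes this specific: "MTs will focus primarily on delivery and teacher training and support, while different research team members will conduct data collection, evaluation, and analysis". It adds adaptation logbooks and an independent project member who oversees all processes.

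Section 2.5, on data collection, agrees: "team-members (other than MTs) will collect the data at each phase of the intervention".

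Section 2.4.2, on classroom delivery, says of the same staff that "MTs will oversee all sessions and assist teachers where needed". It closes by stating that "both quantitative and qualitative data will be collected by the MTs, before, during and after the intervention".

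Section 2.5.3 says that "MTs will organize semi-structured interviews or focus groups, inviting participation from students and teachers". Only the interviews of the MTs themselves go to another project member.

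Section 2.7 says: "Interviews/focus groups will be audio-recorded, transcribed, and analyzed thematically by the MTs".

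**The concern.** The separation of roles in section 2.2.1 is a safeguard against bias, offered because the MTs are close to the intervention at every step. They adapt the material (2.3), lecture at the schools to win parental support (2.2.3), train the teachers (2.4.1), oversee fidelity (2.2) and attend the sessions (2.4.2). Two later sections withdraw that safeguard without saying so.

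Most of what is measured is self-report: tobacco use, susceptibility, intentions and perceived usefulness from students (2.5.1), and views on feasibility, acceptability and potential effectiveness from teachers and students (research question 2). Respondents may answer more favourably to people who run the program, and people who built a program may read comments on it generously. Section 3.1 confirms that there is no control group, so such a shift could not be separated from an effect. Section 3.1 does not list evaluation by the trainers among the limitations, so a reader of the results would assume the separation promised in 2.2.1 was in place.

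**Working it through.** No formula applies. The point concerns who does which task and depends on no alpha, power, effect size or sample size. The check is to set the assignments side by side.

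| Task | Assigned to non-MT members | Assigned to MTs |
|---|---|---|
| Data collection | 2.2.1 (different team members); 2.5 (MTs excluded, every phase) | 2.4.2 (both data types, before, during and after) |
| Analysis of interviews and focus groups | 2.2.1 (evaluation and analysis) | 2.7 (thematic analysis) |
| Arranging student and teacher interviews | not stated | 2.5.3 (organize and invite) |
| Conducting student and teacher interviews | 2.2.1 and 2.5, as data collection | 2.4.2, as data collection |
| Interviewing the MTs | 2.5.3 (another project member) | none |
| Quantitative analysis | 2.2.1 | none |

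**Row 1 is a direct contradiction.** Sections 2.4.2 and 2.5 each cover all the data and the whole study period. There is no data type or time point that one leaves to the other, so no division of labour satisfies both.

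**Row 2 is a direct contradiction.** Section 2.2.1 gives analysis to people other than the MTs, and 2.7 names only the MTs for the thematic analysis.

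**Can the softer wording in 2.2.1 reconcile them?** The phrase "those adapting the training are not solely responsible for its evaluation" would permit shared responsibility, and the statement that MTs concentrate primarily on delivery would permit some other work. But the second half of that same sentence gives collection, evaluation and analysis to different people. Section 2.5 excludes MTs from collection without qualification, and 2.7 names no one besides the MTs. The soft wording closes neither gap.

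**Row 3 is not a contradiction in itself.** Organizing and inviting can be logistics, which is compatible with 2.5. The sentence becomes a problem only because 2.4.2 and 2.7, on either side of it, suggest that the MTs' part goes further.

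**Which research question is exposed?** For research question 1, section 2.5.1 says the student questionnaires are self-administered, which limits the collector's influence on answers. Section 2.4.2 also has the MTs collecting before as well as after the sessions, so some of any influence could be present at baseline and partly cancel in the pre-post difference. For research question 2, the data are spoken opinions of the program, gathered after it ends and then interpreted. Neither protection applies.

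**The case against.** The strongest reply is that the intended plan is clear. Section 2.5 is the dedicated data-collection section and excludes the MTs outright. Section 2.2.1 states the rule and its reason. The sentence in 2.4.2 is one closing remark in a section about delivery, and may be a remnant. On this view there is a slip of wording and no design fault. The study also calls itself a pilot and exploratory, provides logbooks and an independent overseer, and discloses the missing control group.

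Much of this stands. A reader might infer that the MTs will in fact collect the students' self-reports; the document does not support that, because it says both things. A reader might also infer from 2.5.3 that the MTs choose the individual respondents or conduct the interviews; the text says only that they organize and invite. Nor does anything assign the quantitative analysis to the MTs.

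Two things do not fall away. The reply about a stray sentence covers only 2.4.2: section 2.7 separately names the MTs as analysts of the interviews, and no later section corrects it. And an overseer who receives updates and gives feedback does not replace separate collectors and coders.

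**Conclusion.** The point holds as an internal contradiction, in two places: data collection (2.4.2 against 2.2.1 and 2.5) and qualitative analysis (2.7 against 2.2.1). It should be corrected before data are collected, because who gathered the data cannot be changed afterwards.

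The consequence is conditional. If 2.4.2 and 2.7 are followed, the evaluation of research question 2 loses the independence that 2.2.1 promises. Research question 1 is affected less, for the reasons given above. If 2.2.1 and 2.5 are followed, the concern disappears.

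The size of any bias cannot be estimated from the document. It is tempting to compare it with the smallest pre-post change the study could detect and to conclude that a shift of that size would look like an effect. That would need a design effect the document does not give, and a shift confined to follow-up, whereas 2.4.2 describes MT collection at baseline too. No such figure is offered here.

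**What to change.** Three changes of wording:

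1. **Section 2.4.2:** state that quantitative and qualitative data are collected by team members other than the MTs, in line with 2.5.
2. **Section 2.7:** assign the coding and theme development to the non-MT researchers described in 2.2.1.
3. **Section 2.5.3:** state that the MTs' organizing is limited to logistics, and that non-MT members conduct the student and teacher interviews and focus groups.

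One role should then own each data stream and each analysis across 2.2.1, 2.4.2, 2.5, 2.5.3 and 2.7.

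The cost is mainly wording, because 2.2.1 and 2.5 already give these tasks to other team members. The document does not show how many such members are available. The workload they take on is modest: at the minimum numbers in 2.5.3, six schools with 3–4 students and 2–3 teachers each give 18–24 students and 12–18 teachers, or 30–42 respondents.

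Further steps, such as random selection of invitees, fidelity checklists completed by non-MT staff or a log of MT assistance in class, go beyond this contradiction and are not needed to resolve it.
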